#### Test des Deux Barrages (T2B)

The T2B is a commonly applied assessment in clinical neuropsychology to test selective attention. The original version consists of two parts, one time-independent, the second limited to 10 minutes. For the purpose of this study, only the latter will be applied. The test is presented on a large A3 sheet that displays two symbols in the header line and a 40 × 25 matrix with a total of 1000 randomly assorted symbols similar to those in the header line. Only a few of the matrix symbols are identical to the header symbols. The participant is instructed to mark only identical ones. Test duration is 10 minutes. After every minute, the assessor notes the progress of the participant indicating the line and column. After 10 minutes, the amount of falsely marked symbols is counted using a template solution. The task is to work as quick and accurately as possible. The parameters to quantify this are: time needed (if less than 10 minutes), total amount of correct markings per minute, amount of omitted symbols per minute, amount of wrong markings per minute, sum of errors per minute (omitted or wrong marking), percentage of errors, and range of performance (highest frequency of correct markings per minute to lowest frequency of correct markings per minute).

#### National Institute of Health Stroke Scale (NIH-SS)

The NIH-SS is a standardised assessment of neurological functions in the acute phase of stroke [34]. It is generally used to quantify improvement of the patient’s neurological impairments on 15 items in 11 areas of different neurological status. The administering medical doctor observes the patient and rates each item on an ordinal scale with three to five levels. A maximum of 42 points can be achieved, which would correspond to severe neurological impairment. The NIH-SS will be recorded once to allow classification and description of the severity of stroke of the included patients. It is generally provided by the referring hospital. If not, the treating neurologist may reconstruct it retrospectively [35].

#### Modified Barthel Index (MBI)

The MBI assesses impairment of daily activities in patients with neurological disorders and takes into account available support (personal or device-specific) [36]. The scale rates motor and cognitive functions on a five-point Likert scale (0–4, the higher the less dependent).

#### EuroQol Questionnaire (EQ-5D)

The EQ-5D is a generic self-report instrument for use as a measure of health outcome [37]. Applicable to stroke, but also other health conditions [38], it provides a simple descriptive profile and a single index value for health status.

### Data collection methods and management

Data will be collected on digitalised Case Report Forms (e-CRF) that will resemble the paper forms approved by the ethics committee (p-CRF). Data will be transferred from the output files and assessment forms to the e-CRFs and will not be part of the patient’s case history. Forthwith, only a participant ID will be connected to the data. The CRF will be transferred to the data administrator of the Data Control Centre (DCC, party A) after being signed (digitally) by the clinical inspector. The DCC will verify consistency, completeness, and accuracy of submitted data forms. All participating trial centres will be contacted by the DCC in case of uncertainties regarding the submitted data and the DCC will inform all trial centres on the status of the database.

All data is treated with utmost confidentiality and made anonymous to anyone outside the study (except the ethics committees during audit). Any further analyses will only refer to ID numbers. The key will only be accessible to study personnel with a password for the protected local drive where data is saved. All data and related documents remain archived for 10 years at each study centre before being shredded. All trial centres will receive anonymous copies of all data in order to promote dissemination of study results.

Entering data forms and general information about obtaining data was covered during the training session prior to study commencement.

### Statistical methods

All allocated subjects will be analysed with the available data, i.e. on the basis of intention-to-treat (ITT). The last observation carried forward method will be applied in case of missing data.

A significance level of 95 % (two sided *p* values alpha <0.05) will be used. After examining the data for normality (the Kolmogorov-Smirnov test) the outcome measures will be analysed using ANOVA (assuming normal distribution) or Kruskal-Wallis (nonparametric test). Demographic characteristics and other baseline values will be described using descriptive statistics for each group. Significant group interactions will be analysed post hoc. The Bonferroni method will be used to appropriately adjust the overall level of significance for multiple outcomes. A statistician blinded to study groups will conduct statistical analysis.

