**Methods/Design:**

An international multicentre, single-blinded, randomised controlled pilot trial will be conducted. In a 1:1:1 ratio, 60 inpatients with post-stroke cognitive dysfunction will be randomly allocated into either the acupuncture group, the computer-assisted cognitive training group, or the ACoTrain group in addition to their individual rehabilitation programme. The intervention period of this pilot trial will last 4 weeks (30 minutes per day, 5 days per week, Monday to Friday). The primary outcome is the test battery for attentional performance. The secondary outcomes include the Trail Making Test, Test des Deux Barrages, National Institute of Health Stroke Scale, and Modified Barthel Index for assessment of daily life competence, and the EuroQol Questionnaire for health-related quality of life.

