## Methods

### Study design and setting

The study is designed as an international multicentre study with randomised, controlled group comparators and blinded assessors. The study will be an explorative pilot study with three parallel treatment groups: computer-assisted cognitive training (CaCT), acupuncture (AP), and intervention that incorporates CaCT and AP (ACoTrain, ACT). Three neurological rehabilitation clinics from three different countries will be involved in recruitment, treatments and assessments. Each clinic will aim to recruit 20 inpatients currently recovering from their clinically first-ever stroke. Attention performance will be assessed as the primary study outcome in all groups before and after a 4-week intervention. The multicentric body of trial centres consists of specialised neurological rehabilitation centres from China (Fujian University of Traditional Chinese Medicine, A), Switzerland (Reha Rheinfelden, B), and Germany (m&i Fachklinik Herzogenaurach, C). Fig. 1 illustrates the flow chart of patient allocation and study design.

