### Sample size

The international setting is thought to increase the generalisability of the study results, as the study sample will include patients with different cultural background. However, it is also expected that high heterogeneity regarding affected cortical areas and functional ability within the study groups of stroke patients will occur. The number of participants will therefore not suffice to conduct a full-scale study but are thought to provide a basis for estimation of the effects and planning of a larger follow-up study, if proven feasible.

The aim is to recruit 20 patients per clinic (N_total_ = 60). The results will be used to compute sample size and conduct a power calculation to plan the full-scale follow-up study.

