### Inclusion criteria

In order to properly understand and apply the training methods and the content of the study, the patients are required to have some level of cognition. To assess the minimum level required, the Montreal Cognitive Assessment (MoCA) [20] will be applied at baseline (BL). Patients eligible for the trial must comply with all of the following criteria prior to randomisation: (1) clinically first-ever stroke, diagnosis confirmed by CT or MRI; (2) aged between 18 and 80 years old; (3) clinically confirmed attention deficits (>1SD below mean of age-matched norm in at least one subtest of the Test for Attentional Performance, TAP); (4) inclusion within 6 months after stroke onset; (5) conscious, stable physical condition; and (6) given oral and written consent confirmed by the signature of the patient.

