### Interventions

All study interventions are described in Table 2 using the Template for Intervention Description and Replication checklist and guide, known as TIDieR. Patients will be evenly allocated to CaCT, AP, or ACT. All groups will additionally receive conventional neurorehabilitative treatment as prescribed by each clinic. The experimental intervention of this trial will be added to the existing therapy plan as a daily treatment of 30 minutes for 4 weeks (Monday to Friday). Every treatment will be documented on the therapy documentation sheet (standardised for each trial centre).

**Table 2 Tab2:** Description of study interventions based on the TIDieR template^*a^

Item	Computer-assisted cognitive training	Acupuncture	ACoTrain
1 Short name	Ca CT	AP	ACT
2 Why	Main objective is to evaluate the effects of computer-assisted cognitive training CaCT compared to AP on the outcomes of attention assessments		
	Second objective is to test the effects of a combined cognitive intervention that incorporates CaCT and AP		
3 What: materials	Ca CT (RehaCom, Hasomed Inc., Germany, http://www.hasomed.de) will be conducted in the study. Patients will sit in front of the RehaCom system. The training program will be displayed on the computer screen and they also can hear the sound feedback from the audio system. According to different training programs, patients will press a special RehaCom keyboard with large buttons to react	Acupuncture needle, which is single use, φ 0.35 × 40 mm, will be used for acupuncture treatment. The angle of insertion is approximately 10°–20° (between needle and scalp), the needle should be inserted to a depth of approximately 0.3–0.5B-cun	For the combined group, patients will receive AP and CaCT combined, i.e. the CaCT will be performed while the needles are inserted

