### Outcome assessment

Outcomes will be measured once before intervention (T0) and once after intervention (T1, at 4 weeks) in a 1- to 1.5-hour assessment. Assessments will be conducted by a trained and experienced therapist or neuropsychologist blinded to group allocation. None of the assessors will participate in the treatment. The study will use a number of standardised scales to assess functional changes. At baseline, additional assessment of basic cognitive functioning will be administered for classification of the included patients.

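### With only a baseline and one post-treatment assessment, last observation carried forward enters zero change for every patient missing T1, which can distort the arm contrasts and the planning of the follow-up trial

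*Protocol article*

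**What the plan says.** The Statistical methods section sets the analysis population and one rule for missing values, in consecutive sentences: "All allocated subjects will be analysed with the available data, i.e. on the basis of intention-to-treat (ITT"), and then "The last observation carried forward method will be applied in case of missing data". It gives no second method and no sensitivity analysis.

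The Outcome assessment section sets the schedule: "Outcomes will be measured once before intervention (T0) and once after intervention (T1, at 4 weeks"). The Study design and setting section agrees: "Attention performance will be assessed as the primary study outcome in all groups before and after a 4-week intervention". Table 1 marks the primary and secondary variables at one assessment before treatment and one after, with nothing in between.

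Two further statements bear on whether no change is a reasonable value to enter. Eligibility requires "inclusion within 6 months after stroke onset", and the Interventions section says "All groups will additionally receive conventional neurorehabilitative treatment as prescribed by each clinic".

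The Sample size section says that the results will be used for the sample size and power calculation of a full-scale follow-up study.

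**The concern.** Carrying an observation forward needs an earlier post-baseline value. Here there is none. For a patient without T1 the only value available is T0, so the rule amounts to baseline carried forward and fixes that patient's change at exactly zero. In patients early after stroke who are all in rehabilitation, zero is not a neutral guess. The imputed values are then analysed as if observed.

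Two things are at stake. The first is the comparison between arms, which can be shifted or shrunk according to how many patients miss T1 in each arm. The second is the pilot's stated use: an SD, and perhaps a contrast, taken from data filled in this way would be carried into the size of the follow-up trial.

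**Working it through.** **The plan's own figure.** The Sample size section gives "The aim is to recruit 20 patients per clinic (N_total_ = 60"). Three clinics × 20 = 60, and 1:1:1 allocation gives 60 / 3 = 20 per arm. The target rests on recruitment, not on a power calculation. No effect size, SD, dropout or expected recovery is stated, so every other input below is an assumption.

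**Assumptions.** A T-score-like scale with SD 10 at both times; T0–T1 correlation 0.7 (range 0.6 to 0.8); mean 4-week recovery m = 5 points (range 3 to 8); share missing T1 p = 15% (range 10% to 20%); T1 missing at random. The article reports TAP in milliseconds and percentile ranks, so the relative results matter more than the points.

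**Contrast.** An arm with mean change m and share p missing has mean (1 − p) × m under the rule.
- Unequal dropout, no true difference: false contrast = (p2 − p1) × m. With 5% against 20% missing (1 against 4 of 20 patients), 0.15 × 5 = 0.75 points; for recovery of 3 to 8, 0.45 to 1.2.
- Equal dropout, true difference: the contrast is multiplied by 1 − p, so by 0.85 at 15%. A simulation of 20,000 trials with 20 per arm and a true contrast of 0.5 SD gave 0.453 at 10% and 0.397 at 20% missing, against 0.45 and 0.40 by formula.
- Equal dropout, equal mean change: (1 − p)m − (1 − p)m = 0, so no bias.

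**SD, if change is analysed.** True variance s² = 2 × 100 × (1 − 0.7) = 60, so s = 7.75. Under the rule, variance = (1 − p)s² + p(1 − p)m² = 0.85 × 60 + 0.15 × 0.85 × 25 = 54.2, so SD = 7.36. The variance ratio is 54.2 / 60 = 0.903. The SD is too small when m²/s² < 1/(1 − p) and too large above that.

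**SD, if the T1 value is analysed.** Variance = 100 + p(1 − p)m² = 100 + 0.1275 × 25 = 103.2, so SD = 10.16 instead of 10. The direction is reversed.

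**Follow-up sample size, change analysed.** The required number is proportional to variance / contrast².
- Only the SD taken from the pilot, target difference set elsewhere: ratio 0.903, about 10% too small. Over the assumed ranges the extremes are 0.8 × (1 + 0.2 × 9/80) = 0.818 and 0.8 × (1 + 0.2 × 64/40) = 1.056.
- SD and contrast both taken from the pilot: ratio 0.903 / 0.85² = 1.25, about 25% too large. In general it is (1 + p m²/s²)/(1 − p), which exceeds 1 for any p > 0. Over the ranges it runs from (1 + 0.1 × 9/80)/0.9 = 1.12 to (1 + 0.2 × 64/40)/0.8 = 1.65.

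A separate check in SD units (true contrast 0.5, two-sided 0.05, 80% power) needs 63 per arm. With 20% missing and a comparator change of 0.3 SD, planning gives 54 per arm from the distorted SD alone, or 85 from the distorted SD and contrast together.

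**Size against the pilot's imprecision.** The standard error of an arm contrast is 7.75 × √(2/20) = 2.45, so 0.75 is about 0.3 standard errors. The SD shift from 7.75 to 7.36 is 5%, while a 95% interval for a pooled SD on 57 degrees of freedom runs from about −15% to +22%.

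**The case against.** The strongest reply accepts the mechanism and disputes the consequences. This is an exploratory pilot; the documents predict no dropout; and on plausible figures the bias is a fraction of the sampling error. That stands, and it limits the severity. It does not rescue the rule, because sampling error is reported in an interval and this bias is not.

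Several stronger readings are tempting but not supported:

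- *The rule always biases the contrasts.* It does not when dropout and mean change are equal across arms and missingness is random.
- *The follow-up trial will be too small.* A reader might infer this from the reduced SD of change. It requires a target difference set outside the pilot. The Sample size section also speaks of a basis for estimating the effects, and if the contrast is taken from the pilot the error runs the other way.
- *The rule shrinks the SD.* The Statistical methods section does not say whether change or T1 is analysed. If T1, the SD is inflated.
- *Patients miss T1 because they recovered and went home early.* The documents say nothing about early discharge, and deterioration is as possible.
- *The rule contradicts the sentence before it.* Analysing all allocated subjects with available data can be read as keeping everyone randomised, with carrying forward as the means. The wording is loose and should be tidied, but it is not a clear contradiction.

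**Conclusion.** The concern holds in a conditional form. That the rule enters zero change for each patient missing T1 follows from the article's own schedule and needs no assumption. How much it matters depends on dropout and recovery, which the documents do not give. Under the assumed figures, unequal dropout of 5% against 20% produces a false contrast of 0.75 points, and equal dropout of 15% removes 15% of a true contrast. The follow-up sample size is then about 10% too small or about 25% too large, depending on what is taken from the pilot. With few missing T1 values the effect is small.

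The rule should be fixed before analysis: it is the only one stated for missing data, it applies to the primary outcome, and it feeds the estimates that the pilot is meant to supply. It does not invalidate the trial, and a must-fix rating would overstate it. Severity: SHOULD-FIX.

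**What to change.** Replace the carry-forward sentence. The primary analysis should use observed T1 data adjusted for the T0 score. An equivalent likelihood-based model of T0 and T1, or multiple imputation of T1 using arm, centre and T0, would serve as well. State that the SD and contrast used to plan the follow-up trial come from that analysis. Keep baseline carried forward, if at all, as a labelled sensitivity analysis, and reword the intention-to-treat sentence to match.

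The cost is modest. No new data are needed, but baseline adjustment alters the plain ANOVA now stated, and the nonparametric route needs matching wording, so the change goes a little beyond one sentence. Expect slightly more analysis work and slightly wider intervals, since missing values are no longer counted as observed.

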### Randomization and blinding

For the randomisation, restricted randomisation with random block sizes between 3 and 9 (exact size to be determined by an external institution) will be used. This will reduce opportunities for bias and confounding and increases the probability to meet the assumptions of statistical analysis (treatment groups are random samples of population) [21]. Each centre will receive a computer-generated randomisation list (MATLAB 2007b, Mathworks Inc., Natick, MA, USA) from a third-party partner institution, which is elsewise not involved in the study. Sequentially numbered opaque and sealed envelopes will be distributed to each trial centre by a third-party employer, who is not part of the investigating team. The treating therapist will inform the participants after baseline assessment immediately before the first treatment. The assessor remains uninformed about group allocation. Patients will be informed and reminded not to mention the study treatment in front of the assessors.

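### The named ANOVA or Kruskal-Wallis test includes neither baseline adjustment nor centre, and the analysed variable is not defined; a model for T1 with T0 and centre would be more precise at almost no cost

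*Protocol article*

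**What the plan says.** All references are to the protocol article.

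- **Test.** Under Statistical methods, after a Kolmogorov-Smirnov check, "the outcome measures will be analysed using ANOVA (assuming normal distribution) or Kruskal-Wallis (nonparametric test"). The level is two-sided 0.05. Baseline values appear in that section only as something to describe by group.
- **Interactions.** The same section adds: "Significant group interactions will be analysed post hoc". It does not say which second factor interacts with group.
- **Visits.** Outcome assessment sets one measurement before treatment (T0) and one at 4 weeks (T1). NIH-SS is the exception, being recorded once. The Discussion describes the aim in terms of change in attention. No section says which variable enters the ANOVA.
- **Randomisation.** Under Randomization and blinding: "Each centre will receive a computer-generated randomisation list". Block sizes vary between 3 and 9, so allocation is stratified by centre.
- **Size and heterogeneity.** The abstract states: "In a 1:1:1 ratio, 60 inpatients with post-stroke cognitive dysfunction will be randomly allocated". Sample size adds: "The aim is to recruit 20 patients per clinic". It also expects that "high heterogeneity regarding affected cortical areas and functional ability within the study groups of stroke patients will occur".

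**The concern.** The design supplies two strong sources of precision: a baseline score of the same measure for each patient, and a centre factor that allocation already respects. The named tests take up neither as a covariate or stratum, and Kruskal-Wallis on three groups cannot do so.

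This matters because the pilot's declared products are effect estimates and the inputs for the follow-up trial's sample size. With about 20 patients per arm, the standard error of the chance T0 difference between two arms is sqrt(2/20) = 0.32 SD. An analysis of T1 alone carries that imbalance straight into the estimate. Differences between three clinics in three countries go into the error term, although allocation was balanced within them. If the follow-up trial adjusts for baseline and centre, an unadjusted SD from this pilot would overstate the variance it faces.

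Leaving the analysed variable undefined also means that T1 or change could be chosen after the data are seen.

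**Working it through.** **The plan's own figure.** 3 centres x 20 = 60, or 20 per arm at 1:1:1. This agrees. No effect size, SD or power is stated, so there is no power figure to reproduce.

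**Assumed inputs.** The documents give neither the T0-T1 correlation r nor the share c of outcome variance that lies between centres. Both are varied below.

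**Step 1: baseline.** Variance of an arm difference, relative to an ANOVA on T1 (= 1), with equal SDs at both visits:

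- change score, or group-by-time ANOVA with two visits: 2(1 - r)
- analysis of covariance (ANCOVA) on T0: 1 - r²
- ANCOVA against change: (1 - r²) / [2(1 - r)] = (1 + r)/2

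| r (assumed) | Change | ANCOVA | ANCOVA / T1-only | ANCOVA / change |
|---|---|---|---|---|
| 0.3 | 1.40 | 0.91 | 0.91 | 0.65 |
| 0.5 | 1.00 | 0.75 | 0.75 | 0.75 |
| 0.7 | 0.60 | 0.51 | 0.51 | 0.85 |
| 0.8 | 0.40 | 0.36 | 0.36 | 0.90 |

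Dividing 60 by these factors gives the equivalent number of patients in a T1-only analysis. For ANCOVA it is 66, 80, 118 and 167. For change it is 43, 60, 100 and 150. At r = 0.3 a change score is worse than not using T0 at all.

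**Step 2: interval width.** The 95% half-width for one pair of arms, before any Bonferroni correction, is t(0.975, 55) x sqrt((2/20)(1 - r²)), with t about 2.00. It is 0.63 SD unadjusted, then 0.55, 0.45 and 0.38 SD at r = 0.5, 0.7 and 0.8.

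**Step 3: centre alone.** A centre term multiplies the variance by 1 - c. At c = 0.05, 0.10, 0.20 and 0.30, the equivalents are 60/0.95 = 63, 60/0.90 = 67, 60/0.80 = 75 and 60/0.70 = 86.

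**Step 4: error rate when centre is left out.** This was simulated with 3 centres of 20, blocks of 3, 6 or 9 within centre, no treatment effect and 6,000 runs per setting. The nominal level is 5%.

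| c (assumed) | ANOVA | Kruskal-Wallis |
|---|---|---|
| 0 | 5.0% | 4.9% |
| 0.10 | 3.6% | 3.4% |
| 0.20 | 2.5% | 2.4% |
| 0.30 | 1.5% | 1.4% |

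The test is conservative because blocking removes centre variation from the arm contrast while the error term keeps it.

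**Step 5: both together, against T1-only.** The factor is (1 - c)(1 - r²), with c now the centre share of what remains after T0.

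- r = 0.3, c = 0.05: 0.95 x 0.91 = 0.864, equivalent to 69 patients
- r = 0.5, c = 0.10: 0.90 x 0.75 = 0.675, equivalent to 89
- r = 0.7, c = 0.20: 0.80 x 0.51 = 0.408, equivalent to 147

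**The case against.** **T0 may already be used.** A reader might infer that the plan discards the baseline altogether. The documents do not support that. A one-way ANOVA on T1 has no interaction, so the sentence on group interactions needs a second factor, and the Discussion speaks of change. A group-by-time or change-score ANOVA is a natural reading, and both use T0. This stands: the supportable statement is that the use of T0 is undefined and no baseline adjustment is named. The factor could also be centre, which would then be in the ANOVA, but nothing says so and the Kruskal-Wallis branch could not hold it.

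**The loss may be modest.** This stands too. The equivalents of 80 to 167 patients apply only to T1-only analysis at r of 0.5 to 0.8. Against a change score at r = 0.8, the gain is 10% of the variance. Without r and c, a large waste of information is not shown.

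**Centre differences could swamp the treatment contrast.** A reader might infer this, but separate blocked lists keep the arms nearly balanced within each centre. The harm is to standard errors.

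**It is a pilot.** The article calls the study explorative and claims no power. T0, T1 and centre are all recorded, so an adjusted SD could be computed later. That lowers the severity. It does not remove the point, because effect estimates and planning inputs are what the pilot is for.

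**Model terms belong in the analysis plan.** This is partly fair for a condensed article. But the article does name the tests, and one of them cannot take covariates, so this is a stated choice as well as a missing detail.

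**One pooled model does not suit every outcome.** This stands. The Chinese TMT-B is a different test, and TAP is expressed as percentile ranks, which are bounded. With two visits, carrying the last observation forward sets a missing T1 equal to T0, so adjustment does not resolve missing data.

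**Conclusion.** The point holds as a recommended improvement. The named analysis has no baseline adjustment and no centre term, and the variable to be analysed is not defined. ANCOVA is more efficient on either reading of the ANOVA: its variance is 0.91 to 0.36 of T1-only, and 0.65 to 0.90 of change, for r from 0.3 to 0.8. Omitting centre makes a nominal 5% test run at about 3.6% or 2.5% for centre shares of 10% or 20%. These sizes rest on assumed r and c, on equal SDs at both visits for the change-score comparison, and on 20 patients per arm with complete data.

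The consequence is lost precision and a residual SD less suited to planning the follow-up trial. The unadjusted randomised comparison is not biased by these omissions, and no stated power or sample-size figure is wrong.

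**What to change.** Replace the test sentence in Statistical methods with a defined model. For each continuous outcome measured at both visits, T1 = arm + T0 of the same measure + centre (fixed, 3 levels). Report adjusted arm differences with 95% confidence intervals.

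Two provisions should go with it:

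- If residuals are clearly non-normal, as may happen with TAP percentile ranks, use a transformed or rank-based version of the same model in place of Kruskal-Wallis.
- For TMT-B, where the Chinese version is a different test, standardise within centre or analyse by test version. A centre intercept alone does not correct for a different scale.

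The sentence on interactions should either name its second factor or be removed.

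The cost is a few sentences and three degrees of freedom (one for T0, two for centre), leaving 57 - 3 = 54. No new data are needed.
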